## 6.5 Randomization

Eligible participants will be randomly allocated in one-to-one ratio to the atropine only (AT) or atropine plus optical defocus (ATD) treatment groups using the block size of 4. AT group is denoted as A while ATD group is denoted as B. List of possible permutations are AABB, ABAB, ABBA, BABA, BAAB, BBAA. The allocation sequence will be generated by Excel by Principal investigator. The sequence will be stored in an online platform encrypted with password. The access to sequence will only be given to the site coordinator who is unmasked to assign the participants to the interventions.

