### 4.2.2 DIMS lenses

Defocus Incorporated Multiple Segments, DIMS lens is an optical method to control myopia progression (15). It adopts concept of myopic defocus, which a positive-powered lens relative to refractive error of the user is embedded, so the focal plane of the image is cast in front of the retina, which induces a “stop” signal for eye elongation. Myopic defocus has been shown to inhibit myopic eye growth in animal models including in chicks, guinea pigs, tree shrew, and monkeys (16). In DIMS lens, a +3.50D myopic defocus is incorporated in defocus incorporated multiple segments (DIMS) spectacle lenses. DIMS spectacle lenses consist of a central 9-mm optical zone with distant correction which provides a clear distance vision, and it is surrounded by multiple tiny spots of myopic defocus lenses (+3.50D) at periphery. Myopia progression was significantly retarded by about 60% in schoolchildren wearing DIMS spectacle lenses in a 2-year randomized controlled study comparing with no intervention is adopted (8). DIMS spectacle lenses are now commercially available as one of the non-invasive myopic control interventions.

However, none of the currently available intervention completely halts myopia progression and their effectiveness varies between individuals. It is found that the younger the schoolchildren they are, the less effective the myopic control interventions are (12). Therefore, it is crucial to explore treatment strategies that have potential for increased effectiveness and may completely halt myopia progression, thereby avoiding development of high myopia.

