## 6.1 Inclusion Criteria

Participants will be eligible if they are seven to twelve years of age and of Hong Kong Chinese descent. Refractive status requirements are myopia -0.75DS or more in SER in both eyes, astigmatism -1.50D or less in both eyes, anisometropia 1.50D or less in SER. Functional vision requirements are spectacles best corrected monocular VA 0.04 logMAR or better, normal colour vision and normal binocular function. Participants and their parents or guardians must sign and date the informed consent and assent form and they must be willing to comply with all study procedures and be available for the duration of the study. Participants will need to be willing to wear spectacle regularly and put on eye drops daily.

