### 7.2.2 Treatment effects

The effectiveness of myopic control will be calculated as:

1 – (progression therapy) / (progression control)

Unpaired t-test will be used to compare the changes in primary outcomes between two groups. If statistically significant differences in baseline demographic characteristics between groups are found, these significant covariates will also be adjusted in these primary analyses with Analysis of Covariates. In this case, both the unadjusted and adjusted results will be reported. Multiple regression analysis with the primary outcomes at the final visit will act as the dependent variable and independent variables, alongside with the secondary outcomes, will be employed to identify factors that may associate with myopia control effectiveness.

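### Age enters the primary comparison only if the arms differ significantly in age at baseline, and allocation is not stratified by age, so smaller chance age gaps stay unadjusted and precision is lost.

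*Combined protocol and SAP*

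**What the plan says.** **Population.** Section 6.1: "Participants will be eligible if they are seven to twelve years of age". Section 4.2.2, on why better strategies are needed, says that "the younger the schoolchildren they are, the less effective the myopic control interventions are". The Overview makes a similar remark.

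**Allocation.** Section 6.5 assigns children 1:1 to the two "treatment groups using the block size of 4", lists the six possible blocks, and continues: "The allocation sequence will be generated by Excel by Principal investigator". One sequence is described and no stratification factor is named. The Randomization paragraph of the Overview and section 6.13.1 add none. That allocation is unstratified is inferred from this silence; the documents do not use the word.

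**Analysis.** Section 7.2.2: "Unpaired t-test will be used to compare the changes in primary outcomes between two groups". Then: "If statistically significant differences in baseline demographic characteristics between groups are found, these significant covariates will also be adjusted in these primary analyses", by analysis of covariance. It adds: "In this case, both the unadjusted and adjusted results will be reported". The Overview repeats this rule and names age and sex as the demographics compared at baseline. Neither place says which of the two results is primary.

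**The concern.** Blocks of 4 keep the arm sizes equal but do nothing for age. With 56 children per arm, a gap of some months in mean age can arise by chance. If progression depends on age, that gap shifts the treatment difference in that trial.

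The plan's only protection is a significance test on baseline age. That test measures how surprising a gap is under randomisation, not how much it moves the outcome. A moderate gap can pass the test and still matter. Where the test does trigger adjustment, the reader gets two results with no rule for choosing between them. At stake are the precision of the primary estimate and its trustworthiness in a trial that happens to draw a moderate gap.

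**Working it through.** **The plan's own figure.** Section 7.1 gives a difference of 0.384 D, SD 0.56 D, two-sided 5% and 90% power. The effect size is 0.384 / 0.56 = 0.686 (printed as 0.685). A two-sample t-test with the noncentral t distribution gives 46 per arm, with power 90.1% at 0.685. The plan's 46 reproduces. It makes no allowance for covariates.

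**Assumptions.** The documents give no age SD and no slope of progression on age. I take:
- age uniform from 7 to under 13, so SD = 6/√12 = 1.73 years (a narrower 7.0 to 12.0 gives 5/√12 = 1.44);
- a linear slope of 0.05 to 0.20 D per year of age;
- total outcome SD held at the planned 0.56 D.

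**Step 1: size of chance age gaps.** SE of the difference in mean age = SD × √(2/n).
- n = 56: 1.73 × √(2/56) = 0.33 years. The median absolute gap is 0.674 × 0.327 = 0.22 years. The chance of a gap above 0.5 years is about 13%.
- n = 46: 1.73 × √(2/46) = 0.36 years.

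**Step 2: what the baseline test misses.** The largest non-significant gap is t(0.975) × SE.
- n = 56: 1.98 × 0.327 = 0.65 years.
- n = 46: 1.99 × 0.361 = 0.72 years.
- With age SD 1.44 these become 0.54 and 0.60 years.

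At 56 per arm the test fires in about 5% of trials, essentially all of them among the 13% with gaps above 0.5 years. About 5/13 (some 40%) of those gaps are therefore caught and about 60% escape. Simulation of 112 children in blocks of 4 agrees.

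**Step 3: shift in the treatment difference** = slope × gap, also shown as a share of 0.384 D (age SD 1.73).

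| Gap in mean age | Slope 0.05 | Slope 0.10 | Slope 0.20 |
|---|---|---|---|
| 0.22 y (median, 56 per arm) | 0.011 D (3%) | 0.022 D (6%) | 0.044 D (11%) |
| 0.50 y | 0.025 D (7%) | 0.05 D (13%) | 0.10 D (26%) |
| 0.65 y (limit, 56 per arm) | 0.032 D (8%) | 0.065 D (17%) | 0.13 D (34%) |
| 0.72 y (limit, 46 per arm) | 0.036 D (9%) | 0.072 D (19%) | 0.144 D (37%) |

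**Step 4: overall error rate.** Simulation at 46 per arm (10,000 trials, simulation standard error about 0.2 points) gives a type I error for the unadjusted t-test of 5.0% at slope 0.10 and 5.5% at 0.20. Always adjusting gives 5.1% and 4.9%. The plan's conditional rule, taking the adjusted result when it fires, gives 4.8% and 4.4%. There is no material inflation.

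**Step 5: error rate when a gap slips through.** In the roughly 12% of those trials with a gap above 0.5 years that the baseline test missed, unadjusted type I error was 6.2% (slope 0.10) and 12.4% (slope 0.20), against about 4.4% with age in the model. Power was 85% and 80% unadjusted, against 91% and 98% adjusted.

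**Step 6: precision.** Age explains R² = (slope × SD / 0.56)² of the outcome variance: 2.4%, 9.6% and 38% at slopes 0.05, 0.10 and 0.20. Adjustment reduces the SD to 0.56 × √(1 − R²). Power at 46 per arm then rises from 90.2% to 90.9%, 92.8% and 98.5% (90.7%, 92.0% and 96.7% with age SD 1.44). In simulation (4,000 trials) the conditional rule recovers little of this: 90.0% against 92.2% at slope 0.10, and 92.0% against 98.6% at slope 0.20.

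**The case against.** Leaving allocation unstratified is a legitimate choice at this size. Randomisation makes the comparison valid, and the planned SD of 0.56 D already contains whatever variation age causes. At 46 per arm the SE of the treatment difference is 0.56 × √(2/46) = 0.117 D, so the shifts from a 0.5-year gap are all below one SE and can go either way. The slope is assumed. Its top value would need age alone to explain about 38% of the outcome variance. All of this stands. It limits the point to conditional bias and lost precision, and it is why the median gap is shown beside the larger ones.

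Three stronger readings are tempting, and the documents do not support them.
- A reader might infer that any age imbalance passes straight into the primary comparison. It does not: section 7.2.2 adjusts when the age difference is significant, which catches about 40% of gaps above 0.5 years.
- A reader might take the remark in section 4.2.2 as evidence that progression depends on age. It speaks of weaker treatment response in younger children, which is effect modification. The slope used here is a separate assumption.
- A reader might infer that a planned age-subgroup result is compromised. No such analysis is planned, and children within any age band would still be randomised.

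What the objection does not answer is the rule itself. It ignores most moderate gaps, and it leaves two results without a primary one when it fires.

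**Conclusion.** The point holds as a minor, inexpensive improvement. The lack of age stratification does not make the trial invalid or inflate its overall type I error. The weakness is the combination of one unstratified sequence and an age adjustment that depends on a baseline significance test.

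If age is uniform from 7 to under 13, gaps up to 0.65 years (56 per arm) or 0.72 years (46 per arm) go unadjusted. The effect on the estimate depends on the assumed slope. It is small for a typical gap and reaches about a quarter of the planned difference for a 0.5-year gap at the steepest slope considered. The loss of power from not always adjusting runs from under 1 to about 8 percentage points over the same slopes. A shallower slope or a narrower spread of ages at enrolment would shrink all of these figures.

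**What to change.** **Main change.** In section 7.2.2 and the matching Overview text, make the single primary model for each primary outcome (refraction and axial length) an ANCOVA with treatment and continuous age at enrolment, whatever the baseline comparison shows. Name the unadjusted t-test as a sensitivity analysis and drop the significance-triggered rule. Include age in the multiple imputation model as well. This costs one degree of freedom and some redrafting. Age is already collected through date of birth (section 6.9), and the sample size need not change.

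**Optional, only if enrolment has not started.** Stratify the section 6.5 allocation by age band (7–9 versus 10–12), with a separate block list for each. Under the same uniform-age assumption with 112 children, simulation shows the SD of the age gap falling from 0.33 to 0.17 years, and the chance of a gap above 0.5 years from about 13% to about 0.3%. The costs are small:
- up to one incomplete block per stratum, so arm sizes may differ by at most 2 in each;
- the replacement rule in section 6.7 must refer to the list for the child's own stratum;
- section 6.5 (sequence made in Excel) and section 6.13.1 (randomisation through REDCap) must both describe two lists.

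Adjustment alone deals with most of the problem, so the trial need not take this second step.

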## 6.6 Blinding

It is a single-blinded controlled clinical trial. Investigators, including ophthalmologists and optometrists, who are responsible for collection of data related to myopia progression will be blinded to study intervention. Masking subjects and their parents or guardians is not feasible since the lens design of the DIMS lenses and single vision lenses is easy to be detected. A data monitoring committee will be established to review adverse events during the study and ensure the safety of the study participants. He or she is also responsible for allocation of participants to different study groups. The masking procedures fulfil the CONSORT requirements for a single masked randomized clinical trial. The participants will be asked to wear the spectacles in full-time mode. A log sheet or an access to an online platform will be given to the participants, their parents or guardians for recording usage of eye drops. Compliance will be monitored and checked by phone calls and questionnaire.

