### 6.13.1 Eligibility, baseline assessments and randomization

- Screen potential participants through screening questionnaire and acquire contact details.
- Screen eligible participants through eligibility assessment (Case Report Form (CRF) in Research Electronic Data Capture (REDCap)).
- Perform baseline assessment on participants for eligibility (CRF Baseline in REDCap).
- Record refractive history (CRF RxHx in REDCap).
- Randomization of participants via REDCap (Randomization Log in REDCap).

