## 9.5 Data safety and monitoring

Ellenburg et al. (22) provide guidelines for deciding whether or not a data safety monitoring committee (DSMC) needs to be established for a trial . They proposed that if two or more of the following criteria are met, then a DSMC is required:

- The trial is intended to provide definitive information about the effectiveness and / or safety of a medical intervention.
- There is prior data to suggest that the intervention being studied has the potential to induce potentially unacceptable toxicity.
- The trial is evaluating mortality or another major endpoint such that inferiority of one treatment group has safety as well as effectiveness implications.
- It would be ethically important for the trial to stop early if the primary question addressed has been definitively answered, even if secondary questions or complete safety information were not fully addressed.

This trial meets only the first point indicating that an independent DSMC does not need to be established for the trial. However, data safety and regular monitoring will be performed by steering group committee and study management committee. Compliance with the protocol and accuracy in relation to source documents will be evaluated.

An independent monitor will check the existence and correct date for all signed consent forms. The monitor will sample over 10% of all randomized participant to check correct data collection and data entry for the key points of this study, including visual acuity and treatment / control placement. The monitor will confirm collected data on CRFs in REDCap with the source data and check the data entry from the hard copies such as print out data from open-field autorefractor.

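### One printed block size of 4 and a list made by the principal investigator leave allocation partly predictable: up to a third of assignments, for someone who knows the full history

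*Combined protocol and SAP*

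**What the plan says.** Section 6.5 allocates 1:1, with "treatment groups using the block size of 4". It then prints the orders in full: "List of possible permutations are AABB, ABAB, ABBA, BABA, BAAB, BBAA". On who makes the list: "The allocation sequence will be generated by Excel by Principal investigator". The next sentences put the list on a password-protected online platform and limit access to the site coordinator, who is unmasked and assigns participants.

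Section 6.6 says that a data monitoring committee will be set up and continues: "He or she is also responsible for allocation of participants to different study groups". The same section says that families cannot be masked because "the lens design of the DIMS lenses and single vision lenses is easy to be detected". Staff who collect progression data are to be masked.

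Section 6.13.1 has randomization done through REDCap and lists it after the baseline assessment. The schedule in Section 6.12 puts randomization at Visit 0-1 and the dispensing of spectacles at Visit 2. Section 6.3 recruits from two institutions. Section 6.7 lets some randomizations be discarded and the next allocation used.

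No section says that the principal investigator or the site coordinator stays out of recruitment or eligibility decisions. None says that an assignment stays hidden until the baseline record is saved.

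**The concern.** Concealment has to protect the next assignment from anyone who can influence who is enrolled, or when. Three features weaken it here.

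- A constant, published block of 4 lets a person who knows the earlier assignments work out some of the coming ones. With recognisable lenses worn full time, earlier assignments can be learnt by staff who meet the children.
- The restriction of access to the coordinator does not cover the person who made the list. Section 2 describes investigators as masked, yet an investigator generates the sequence.
- The sentence in Section 6.6 gives allocation to someone other than the coordinator named in Section 6.5.

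The risk is selective enrolment: a child's entry could be timed or declined with the next arm in mind. The primary analysis in Section 7.2.2 is an unpaired t-test, adjusted only for baseline demographics that differ significantly. It would not correct for selection on unmeasured progression risk.

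**Working it through.** The plan states no predictability figure, so the check starts from its block design.

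**Inputs.** Block size 4, 1:1, and six listed orders (Section 6.5); 112 participants (Section 7.1). The list is complete: C(4,2) = 6. The number of blocks is 112/4 = 28.

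**Case 1: block boundaries and all earlier assignments known.** An assignment is certain when one arm is used up within the block.
- Positions 1 and 2: never certain.
- Position 3: certain if the first two are alike (AABB, BBAA), 2/6 = 1/3.
- Position 4: always certain.
- Certain share: (1/3 + 1)/4 = 33.3%, or 28 × 4/3 = 37.3 of 112.
- Best guess (the arm with more places left): (1/2 + 2/3 + 2/3 + 1)/4 = 17/24 = 70.8%.

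**Case 2: the most recent assignment not yet visible.** Lenses are dispensed one visit after randomization, so this can happen.
- Position 3: only position 1 is known; never certain; best guess 2/3.
- Position 4: positions 1 and 2 are known; certain if they are alike (1/3); best guess 1/3 + (2/3 × 1/2) = 2/3.
- Certain share: (1/3)/4 = 8.3%, or about 9 of 112.
- Best guess: (1/2 + 1/2 + 2/3 + 2/3)/4 = 58.3%.

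**Case 3: more assignments unseen.** With the last two unseen, nothing is certain and the best guess is (1/2 + 1/2 + 1/2 + 2/3)/4 = 54.2%. With the last three unseen it is 50%.

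**Case 4: the list itself is held.** All 112 are known. This applies to the maker of the list and to its authorised holder.

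**Alternatives.** The fixed blocks are exact, by the method of Case 1. The varying blocks were simulated for a guesser who knows the full history and the possible sizes.

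| Block scheme | Certain share | Of 112 |
| --- | --- | --- |
| Fixed 4 (the plan) | 33.3% | 37.3 |
| Fixed 6 | 25% | 28 |
| Fixed 8 | 20% | 22.4 |
| Random 4 or 6 | about 5.5% | about 6 |
| Random 4, 6 or 8 | about 2.3% | about 2.5 |

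Enlarging a fixed block helps much less than varying it. The table covers certain assignments only; best-guess success under varying blocks was not calculated.

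**The case against.** The strongest reply is that the one-third figure is an upper bound. It needs a person who knows where blocks start and every earlier assignment, in order, before the next child is enrolled. Lens type cannot be seen at the moment of randomization, and the documents do not give the interval between Visits 1 and 2. Two institutions appear to share one list, so staff at one see only part of the sequence, and discarded randomizations make it harder to follow. All of this stands, and the figure is therefore stated as a maximum with the lower cases beside it.

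The plan also has safeguards: encrypted storage, restricted access, unmasked staff for ordering and dispensing, relabelled lenses, and REDCap access that can be limited by role. These protect the list from outsiders. They do not stop deduction from visible lenses, and they do not separate the list's maker or holder from enrolment.

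A reader might infer more than the documents support:

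- *That three sections contradict each other on allocation.* Sections 6.5 and 6.13.1 are compatible: a list can be made in Excel and applied by the coordinator through REDCap. The anomaly is the one sentence in Section 6.6, where the singular pronoun follows a committee and may be an editing slip.
- *That a masked examiner who sees one lens can infer others.* One lens moves a participant known to be in the same block from 1/2 to 2/3, and no further.
- *That fast progressors can be steered to one arm.* The schedule lists no measured progression before randomization, so this would rest on refractive history or other proxies.
- *That the list must be stratified by institution.* No site effect or imbalance is shown, and separate lists would be easier for local staff to follow.
- *That the monitoring committee is part of this problem.* Section 9.5 says "an independent DSMC does not need to be established for the trial", whereas Section 6.6 plans a committee without calling it independent. That needs reconciling, but as a separate matter.

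**Conclusion.** The weakness is real and should be corrected, preferably before enrolment. Its size depends on what a person knows: up to 33% of assignments certain (about 37 of 112, best guess up to 71%) with the full ordered history and block boundaries; about 8% (best guess 58%) if the latest assignment is unseen; nothing certain if two or more are unseen; and all of them for whoever holds the list. The figures assume one list without gaps.

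They measure vulnerability. They do not show that anyone would use the information, and the documents give no basis for a bias in dioptres. Sample size and nominal alpha are unaffected.

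**What to change.** 1. Replace the fixed block with randomly varying sizes, for example 4 and 6, or 4, 6 and 8.
2. Have an existing team member with no role in enrolment or outcome measurement generate the list from a recorded seed and load it into the REDCap randomization already planned. Replace the sentence that gives this task to the principal investigator.
3. State that REDCap releases each assignment only after consent, eligibility and baseline data are saved.
4. Move block sizes and permutations from the circulated protocol to a restricted randomization record, so that the method stays documented.
5. Correct the sentence in Section 6.6 so that it names the same single role for allocation as Section 6.5.

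The cost is protocol wording and REDCap set-up. Final balance may be slightly looser, because the last block may be incomplete. At exactly 112, the worst case is 57 against 55 with sizes 4 and 6 (two unmatched places), or 58 against 54 with a block of 8 (four unmatched places). Section 2 gives the status as not yet recruiting; if enrolment has started, the change can still apply to the remaining allocations, with the switch point recorded.
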